### Pneumococcal vaccination

In the last decades, the need for preventive strategies has driven multiple efforts to develop an effective vaccine, however the existence of more than 90 distinct pneumococcal serotypes has largely complicated the development and evaluation of anti-pneumococcal vaccines. To date, only a 23-valent polysaccharide pneumococcal vaccine (PPV-23) for use in adults and a 7-valent conjugate vaccine for use in infants are available in clinical practice [6-9].

The PPV-23 is generally recommended for high-risk and elderly individuals, but its effectiveness (despite numerous meta-analyses) remains controversial [10-19]. It has been demonstrated that PPV-23 provides considerable protection against invasive pneumococcal disease, while a possible protective effect against pneumonia is discussed [20]. The latest Cochrane Systematic Review supports the use of PPV to prevent IPD in adults, particularly in healthy adults, but it concluded that the meta-analysis does not provide compelling evidence to support the routine use of PPV to prevent pneumonia [18].

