### Rationale for sample size

The annual incidence of CAP in older adults in the study area is estimated at approximately 10 per 1000 person-year based on prior population-based studies among elderly people in the same study area [34,35]. Incidences of AMI and stroke are estimated in 8 and 12 cases per 1000, respectively, in Spanish population [36,37]. Thus, considering a pneumococcal vaccine coverage of approximately 50%,[31] with a p = 0.05 (two-tailed) the size of the study cohort (N = 27,000 individuals followed during a 30-month period) has an statistical power of 80% to detect a posible vaccination effectiveness of 20% against CAP, a 23% against AMI, a 18% against stroke and a 14% against the combined end-point AMI/stroke.

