### Main outcomes and definitions

The primary endpoints of the *CAPAMIS Study *will be the ocurrence of CAP (hospitalised or outpatient), hospitalisation for AMI, stroke and death from any cause. Table 1 shows definitions and criteria used in collecting primary and secondary outcomes.

**Table 1 T1:** Definitions and criteria used to identify and classify the different endpoints in the *CAPAMIS *Study.

OUTCOMES	DEFINITIONS
**A. Community-acquired pneumonia (CAP)***	Pneumonia will be considered when a new radiological infiltrate is identified in a patient with one major criterion (cough, expectoration or fever) or two minor criteria (dyspnea, pleuritic pain, altered mental status, pulmonary consolidation on auscultation and leukocytosis).

**A1. Hospitalised CAP**	Will be considered those pneumonia cases identified on the basis of the listed primary diagnosis codes in hospital discharge databases (ICD-9-CM codes for pneumonia: 480 to 487.0).

**A2. Outpatient CAP**	Will be considered those CAP cases non-hospitalised, and they will be identified from primary care or emergency visits (not hospitalised) with a code registered for pneumonia in the Emergency Unit discharge codes databases (ICD-9-CM codes: 480 to 487.0) or Primary Care Centers diagnosis database (ICD-10 codes: J10.9, J11.9 and J12 to J18).

**B. Pneumococcal CAP****	Defined as a patient with CAP from whom Streptococcus Pneumoniae is identified by blood culture, sputum culture or urinary antigen.

**B1. Bacteremic pneumococcal CAP**	Will be considered when S. pneumoniae was isolated from blood specimens or other sterile sites.

**B2. Nonbacteremic pneumococcal CAP**	Will be considered when the patients have a typical clinical syndrome of pneumonia without bacteremia (negative or not performed blood culture), but they have a sputum culture that yielded pneumococci with no other likely bacterial pathogens and/or they have positive Binax-NOW Streptococcus pneumoniae urinary antigen test.

**C. Acute myocardial infarction (AMI)**	Defined as a patient hospitalised with diagnosis of acute or recurrent episode of myocardial infarction. Cases will be identified on the basis of the primary and secondary listed diagnosis codes in the hospital discharge database (ICD-9-CM code for AMI: 410). All initially identified cases of AMI will be further validated by checking hospital medical records, and each case will be classified as related or nonrelated with a prior episode of CAP.

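### Table 1 (B2) counts pneumococcal CAP with no blood culture as nonbacteremic, so effectiveness against that subtype may be modestly overstated

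*Protocol article*

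**What the plan says.** In the protocol article, Main outcomes and definitions, Table 1 divides pneumococcal CAP (B) into two subtypes.

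- **B1, bacteremic:** "Will be considered when S. pneumoniae was isolated from blood specimens or other sterile sites".
- **B2, nonbacteremic:** a clinical pneumonia "without bacteremia (negative or not performed blood culture", with the added condition that "they have a sputum culture that yielded pneumococci with no other likely bacterial pathogens and/or they have positive Binax-NOW Streptococcus pneumoniae urinary antigen test".

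No section requires a blood culture. Pneumococcal cases are found through hospital, emergency and primary care codes and through laboratory records. The same section says that active follow-up is not feasible.

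On what the vaccine is expected to do, the Background (Pneumococcal vaccination) states: "It has been demonstrated that PPV-23 provides considerable protection against invasive pneumococcal disease, while a possible protective effect against pneumonia is discussed".

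**The concern.** B2 gives a test that was not done the same meaning as a negative test. B1 needs an organism from blood or another sterile site. A truly bacteremic patient with a positive antigen or sputum result, no blood culture and no other sterile-site isolate can therefore only be placed in B2. Record review cannot correct this, because there is no result to review.

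The cases that move across are of the kind the article says the vaccine prevents. They enter the subtype where, on the same account, protection is in doubt. B2 effectiveness then becomes a blend of two effects, with weights set by local culture practice, which a reader of the results could not see. B1 loses the same cases, and with them precision.

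**Working it through.** **The plan's own figure.** The article gives no power or event count for B2. The nearest figure is 80% power for 20% effectiveness against CAP. Its inputs are a CAP rate of "approximately 10 per 1000 person-year", vaccine coverage of about 50%, 27,000 people followed for 30 months, and a two-sided 0.05 level.

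- Person-years before losses: 27,000 × 2.5 = 67,500. CAP events at 10 per 1000: 675.
- Two proportions, 13,500 per group, 0.025 against 0.020: power 79.1%.
- Schoenfeld formula: 78.5% with 608 events (10 per 1000 taken as the unvaccinated rate), 82.6% with 675 (taken as the overall rate).

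The stated power is reproduced. It does not bear on B2, but it supplies the event count used below.

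**Model for B2.** None of the following inputs is in the documents:

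- b: bacteremic share of pneumococcal CAP in the unvaccinated, 10% to 30%.
- q: share of bacteremic cases with no blood culture but positive sputum or antigen, relative to detection of nonbacteremic cases, 10% to 50%. It is taken as equal in both vaccination groups.
- VEb: effectiveness against bacteremic disease, 40% to 75%.
- True effectiveness against nonbacteremic disease: 0.

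Relative B2 incidence is (1 − b) + qb in the unvaccinated and (1 − b) + qb(1 − VEb) in the vaccinated. Hence:

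apparent VE against B2 = qb·VEb / [(1 − b) + qb]

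| b | q | VEb | Calculation | Apparent VE |
|---|---|---|---|---|
| 10% | 10% | 40% | 0.004 / 0.91 | 0.4% |
| 20% | 30% | 60% | 0.036 / 0.86 | 4.2% |
| 20% | 40% | 60% | 0.048 / 0.88 | 5.5% |
| 30% | 50% | 75% | 0.1125 / 0.85 | 13.2% |

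If every bacteremic case went uncultured (q = 100%), the formula reduces to b × VEb, which is 4.0% to 22.5%. If not-cultured cases are kept out of B2, the qb term vanishes and apparent VE is 0 in this model.

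**Effect on B1 with equal culturing.** At b = 20%, VEb = 60% and 40% not cultured, B1 is 0.20 × 0.6 = 0.12 in the unvaccinated and 0.08 × 0.6 = 0.048 in the vaccinated. The ratio is 0.4, so B1 effectiveness stays at 60%, but 40% of its cases are lost.

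**Chance of a false significant result for B2.** The Background attributes about 50% of CAP to pneumococcus. If every such case were detected, B would hold at most 675 × 0.5 ≈ 338 events, and B2 about 246 to 321 over the ranges above. The two-sided chance of significance then rises from 5% to between 5.0% and 22.5%; it is 6.5% in the 4.2% case. If pneumococcus is found in only 20% of CAP (an assumption), the range is 5.0% to 11.8%.

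**Unequal culturing.** Take b = 20% and VEb = 60%, with 20% of unvaccinated and 60% of vaccinated bacteremic cases not cultured. B2 is 0.80 + 0.20 × 0.2 = 0.84 in the unvaccinated and 0.80 + 0.08 × 0.6 = 0.848 in the vaccinated. Apparent VE is 1 − 0.848/0.84, about −1%. In this model the sign turns once the vaccinated-to-unvaccinated ratio of not-cultured fractions exceeds 1/(1 − VEb) = 2.5.

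**The case against.** The case for leaving the definition alone has real weight.

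- **The subtype is not central.** The primary endpoints are CAP, AMI, stroke and death. The Objectives section does not mention bacteremic or nonbacteremic disease. A reader might infer that the rule compromises the study's answer on pneumonia. It does not: what the Abstract and Discussion promise to clarify is the effect on CAP overall, and neither CAP nor total B depends on the B1/B2 split. This stands.
- **A missing culture is not enough to enter B2.** A reader might infer that every patient without a blood culture is classed as nonbacteremic pneumococcal CAP. The sputum or antigen requirement rules that out. It narrows the route but does not close it.
- **The direction is conditional.** A reader might infer that the rule always favours the vaccine. The documents do not say how culturing varies with vaccination status, and the example above reverses the sign. The article does say that centres apply broadly similar diagnostic checklists. That makes equal culturing a reasonable starting point, but equal culturing is the very condition under which the upward bias appears.
- **The size is small and assumed.** With 321 events the standard error of the log hazard ratio is about 2/√321 = 0.11, so a shift of 5.5% is about half a standard error. This stands.
- **Restricting B2 to cultured patients has its own bias.** Membership would then depend on a clinician's decision to culture, which may follow severity or care setting. This also stands, and it argues against replacing B2 outright.
- **The cases may be separable later.** Record review covers laboratory data and laboratory records are used, so the split could be made at analysis. That shows the fix is cheap. As written, the definition still merges the two groups.

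**Conclusion.** The point holds as a limited misclassification in a subtype endpoint. B2 as defined takes in bacteremic cases that were never tested, and B1 loses them. Apparent effectiveness against B2 is biased upward on two conditions: the vaccine protects more against bacteremic than nonbacteremic disease, as the Background supposes, and culturing is similar in both vaccination groups.

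Over the assumed ranges the bias is about 0.4% to 13%, with middle cases of 4.2% and 5.5%. Bacteremic share, non-culture rate and effectiveness against bacteremic disease are all assumptions. The stronger reading, that the rule is likely by itself to produce a convincing false finding of protection, is not supported: the false-positive chance in the 4.2% case is 6.5% against a nominal 5%, even with the most generous event count.

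**What to change.** In Table 1, split B2 into two classes: blood culture negative, and blood culture not performed (bacteremia status unknown). Keep both in B. Report effectiveness against B2 with and without the not-cultured cases, and report the proportion of pneumococcal CAP cases cultured, by vaccination group. That proportion lets a reader judge whether the equal-culturing condition is plausible.

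The cost is a short change to Table 1 and a few extra lines in the results. Whether a culture was taken should be recoverable from the record review and laboratory data already planned. No new data source is needed, and the primary analysis is unchanged.

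The downside is that the culture-negative subset is smaller and is selected by the decision to culture. Its result should stand beside the combined B2 result and not replace it.

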### Epidemiological link between pneumonia and acute vascular events

For several decades, there has been data that chronic inflamation can promote atherosclerotic disease,[21] and in recent years some studies have also found data supporting the fact that acute infections (especially influenza and pneumonia) are associated with a transient increasing risk of acute vascular events [22-25]. In fact, it has been reported that a combination of the diagnosis of pneumonia and myocardial infarction is relatively common among patients hospitalised with severe pneumonia [24,25]. Thus, given this data, it has been suggested that pneumococcal vaccination could perhaps protect patients from cardiovascular events [26-28].

Following this, a recent case-control study conducted in Canada has reported a 47% reduction in the risk of acute myocardial infarction (AMI) among subjects who had received the PPV-23, however, the posible cardioprotective effect of pneumococcal vaccination has not still been proved [26].

Theoretically, pneumococcal vaccination could protect against acute cardiovascular events by an indirect effect preventing pneumonia (as the latter has been shown to trigger myocardial infarction), although a direct effect of pneumococcal vaccination on oxidized low- density lipoproteins can not be excluded. In fact, animal experiments have shown that pneumococcal vaccination reduces the extent of atherosclerotic lesions and it has been hypothesized that antibodies directed against Streptococcus pneumoniae would also recognize oxidized low-density lipoprotein and impede the formation of foam cells [29].

The posible effectiveness of PPV-23 to prevent myocardial infarction, if it exists, probably has been overestimated in the aforementioned Canadian report; however, given the prevalence of heart disease worldwide, even a modest protective effect (epidemiologically plausible) would translate into a considerable benefit at the population level [30]. Thus, prospective validations (which will determine whether the cardioprotective effect of vaccination is real and better estimate its true protective efficacy) are greatly needed.

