** Pneumococcal CAP will initially be identified on the basis of ICD-9-CM codes for pneumococcal bacteraemia (codes 038.0, 038.2, 041.0, 041.2) or pneumococcal pneumonia (code 481) in the Hospitals and Emergency discharge diagnosis databases and ICD-10 code for pneumococcal pneumonia (code J13) in the Primary Care visits diagnosis databases. Laboratory records will also be used to identify cases of pneumococcal infections not detected in ICD-9-CM or ICD-10 discharge codes.

The occurrence of CAP will be established on the basis of an acute respiratory illness, with evidence of the presence of a new infiltrate in a chest radiograph.

Outpatient CAP will be identified from primary care or emergency visit (not hospitalised) with a code registered for pneumonia in the PCCs diagnoses databases (ICD-10 codes: J10.9, J11.9, J12 to J18) or in Emergency discharge databases (ICD-9-CM codes: 480 to 487.0). Hospitalisations for CAP will be identified on the basis of the listed primary diagnosis codes in the hospital discharge databases (ICD-9-CM codes 480 to 487.0).

All cases of CAP (hospitalised and outpatient) must be radiographically confirmed and validated by checking the clinical record with the use of a standardized data-collection instrument (which includes sociodemographical, clinical, exploratory, analytical and radiographical data at the time of diagnosis). CAP will be considered if, on conclusion of the medical record review, the physician reviewer verified this diagnosis and it was not a readmission, a nosocomial pneumonia or another diagnosis. Pneumonia severity index (PSI) and the simpler severity rule CURB-65 will be calculated according to criteria described in classical studies [38,39].

Hospitalisation for AMI will be initially identified on the basis of listed primary and secondary diagnosis codes in the reference hospital discharge database (ICD-9-CM code: 410).

Hospitalisation for stroke will also be initially identified on the basis of the listed primary and secondary diagnosis codes in hospital discharge databases (ICD-9-CM codes 430 to 437). Ischaemic strokes (codes 433, 434, 436 or 437) and hemorrhagic strokes (codes 430 to 432) will be considered, but transient ischemic attacks (code 435) will be excluded for the analyses.

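### Hospitalised CAP is searched by primary discharge code only, so non-pneumococcal CAP admitted under another principal diagnosis has no stated route into the endpoint

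*Protocol article*

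**What the plan says.** Two places in the protocol article fix how hospitalised CAP is found, and they agree. The text under Main outcomes and definitions reads "Hospitalisations for CAP will be identified on the basis of the listed primary diagnosis codes in the hospital discharge databases", with ICD-9-CM codes 480 to 487.0. Table 1, A1 reads "Will be considered those pneumonia cases identified on the basis of the listed primary diagnosis codes in hospital discharge databases".

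The two vascular endpoints are searched more widely. For AMI: "Hospitalisation for AMI will be initially identified on the basis of listed primary and secondary diagnosis codes in the reference hospital discharge database". For stroke: "Hospitalisation for stroke will also be initially identified on the basis of the listed primary and secondary diagnosis codes in hospital discharge databases".

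Four further provisions matter:
- Outpatient CAP (Table 1, A2) is limited to patients who were not admitted.
- Data sources says that record review validates cases first identified by code.
- CAP must be radiographically confirmed and is accepted only if "the physician reviewer verified this diagnosis and it was not a readmission, a nosocomial pneumonia or another diagnosis".
- Pneumococcal CAP (Table 1, B and its footnote) has its own search: bacteraemia codes, pneumococcal pneumonia codes and laboratory records. No primary-code limit is stated there.

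**The concern.** CAP is a primary endpoint. A patient who has community-acquired pneumonia but is discharged with AMI, stroke or respiratory failure as principal diagnosis is not A1, because the pneumonia code is secondary. Nor is the patient A2, because there was an admission. Record review removes false positives and does not look for missed cases. Unless the pneumonia is shown to be pneumococcal, no stated route brings it in.

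This bears on the study question. The Background says that "a combination of the diagnosis of pneumonia and myocardial infarction is relatively common among patients hospitalised with severe pneumonia", and vascular events following pneumonia are a stated objective. AMI and stroke charts are reviewed and labelled CAP-related or not by time since pneumonia onset. A reviewer could correctly label an AMI as CAP-related while the pneumonia behind it is not a CAP event. The article does not say how such a case is handled.

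At stake are CAP events and hence power. If the loss differs between vaccinated and unvaccinated people, the CAP hazard ratio is affected too.

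**Working it through.** **Ascertainment routes side by side**

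| Patient | Route in the article | Counted as CAP? |
|---|---|---|
| Pneumonia principal, AMI secondary | A1 for CAP; secondary code for AMI | Yes, and AMI is captured too |
| Pneumonia secondary, pneumococcus identified | B codes and laboratory records | Found; counting as a CAP event is not spelled out |
| Pneumonia secondary, no pneumococcus identified | None: not A1, not A2 | No |
| CAP not admitted | A2 | Yes |

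Only the third row is a clear gap.

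**Inputs** (Rationale for sample size): N = 27,000, so 13,500 per group at 50% coverage; 30 months = 2.5 years; CAP 10 per 1000 person-years; two-sided 0.05; 80% power for 20% effectiveness (HR 0.80).

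**Reproducing the stated power.** For two proportions with n per group and p̄ the mean of p1 and p2:

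Power = Φ{ [|p1 − p2| − 1.96·√(2p̄(1 − p̄)/n)] / √([p1(1 − p1) + p2(1 − p2)]/n) }

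- *10 per 1000 as the unvaccinated rate.* p1 = 0.010 × 2.5 = 0.025 and p2 = 0.8 × 0.025 = 0.020. Events = 13,500 × 0.045 = 607.5. Power = Φ[(0.005 − 0.003538)/0.001805] = Φ(0.81) = 79.1%.
- *10 per 1000 as the overall rate.* Unvaccinated rate = 0.010/(0.5 + 0.5 × 0.8) = 0.01111, so p1 = 0.02778 and p2 = 0.02222. Events = 675. Power = 83.2%.

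The Schoenfeld formula, Φ(|ln 0.8|·√D/2 − 1.96), gives 78.5% and 82.6%. The stated 80% is reproduced.

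**Equal loss in both groups.** The documents give no share of CAP coded only as secondary, so the shares below are assumptions. Multiplying p1 and p2 by (1 − share):

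| Share of all CAP missed | Events (608 / 675 base) | Power for 20% effectiveness |
|---|---|---|
| 0% | 608 / 675 | 79% / 83% |
| 5% | 577 / 641 | 77% / 81% |
| 10% | 547 / 608 | 75% / 79% |
| 20% | 486 / 540 | 70% / 74% |

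These are shares of all CAP, but the restriction touches only hospitalised CAP. If 50-70% of CAP is hospitalised (also an assumption), missing 10% of all CAP means missing 10/70 to 10/50, or 14-20%, of hospitalised cases. Missing 20% of all CAP means 29-40%.

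**Unequal loss.** If a share u is missed in the unvaccinated and v in the vaccinated, apparent HR ≈ true HR × (1 − v)/(1 − u). Illustrative values:
- u = 10%, v = 10%: 0.80 × 0.90/0.90 = 0.80; effectiveness stays at 20%.
- u = 10%, v = 15%: 0.80 × 0.85/0.90 = 0.756; apparent effectiveness 24.4%.
- u = 10%, v = 20%: 0.80 × 0.80/0.90 = 0.711; apparent effectiveness 28.9%.
- u = 10%, v = 5%: 0.80 × 0.95/0.90 = 0.844; apparent effectiveness 15.6%.
- True HR 1, u = 10%, v = 20%: 0.80/0.90 = 0.889; spurious effectiveness 11.1%.

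**The case against.** The restriction is a consistent design choice. Table and text agree, and limiting pneumonia to the principal diagnosis is a recognisable way to keep out hospital-acquired cases, which the authors clearly want excluded. Some admissions with AMI or stroke principal and pneumonia secondary will be pneumonia that began after admission, and these should not count. That stands as an explanation. It is weak as a reason to keep the restriction, because the protocol already requires radiographic confirmation and physician exclusion of nosocomial cases, readmissions and other diagnoses.

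The power figures are also open to challenge, and this stands in full. The shares are assumed. The planning rate comes from earlier studies in the same area, whose ascertainment is not described. If they also used primary codes, the planned power already allows for the loss.

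A reader might infer several stronger things that the documents do not support:
- *Bacteraemic disease is lost.* It has its own codes and a laboratory search with no stated primary-code limit, so these are the best-recovered cases. There is thus no basis for saying that their loss pulls CAP effectiveness toward zero.
- *Outcome B falls outside outcome A.* Row A defines CAP clinically and radiologically; only A1 and A2 depend on codes. A validated B case meets row A. What is missing is an explicit statement that it counts.
- *Pneumonia with AMI is generally missed.* It is missed only when something other than pneumonia is the principal diagnosis. The Background remark concerns patients hospitalised with pneumonia, and where that is the principal code both events are captured.
- *The CAP-related classification fails.* It is made from reviewed hospital records, and nothing says that the pneumonia must first be an A1 event.

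**Conclusion.** The gap is real but narrow: non-pneumococcal CAP admitted under another principal diagnosis does not reach the CAP endpoint as written. A related loose end is that an AMI or stroke can be CAP-related while its CAP is not an event.

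The size cannot be determined from the documents. Under equal loss the hazard ratio is nearly unchanged and the cost is power: about 2 percentage points if 5% of all CAP is missed, 4 points at 10% and 9 points at 20%. It is nil against plan if the planning rate already reflects primary-code ascertainment.

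Bias arises only if loss differs by vaccination status. That is plausible: below age 65 the vaccination programme began with high-risk conditions, and people with comorbidity may more often be admitted under another principal diagnosis. The documents do not quantify it, and its direction could go either way. This is a cheap improvement to ascertainment, not an error that undermines the design.

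**What to change.** - Identify hospitalised CAP from primary and secondary codes 480 to 487.0, as is already done for AMI and stroke with their own codes.
- State that validated outcome B cases, and any CAP found when reviewing an AMI or stroke chart, count as CAP events from their onset date.
- Rely on the planned record review to reject nosocomial cases, readmissions and other diagnoses.
- Keep primary-code-only CAP as a sensitivity definition, and report by vaccination status how many validated cases the wider search adds. That shows directly whether the loss was equal.

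The cost is more charts to screen, some of which will be rejected as nosocomial. AMI and stroke charts are opened in any case.
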